### Randomization

All the relevant information will be presented again to the participants at the baseline visit and the opportunity to ask any questions they may deem appropriate will be offered. After signing the informed consent, inclusion and exclusion criteria will be reviewed again and BPPV will be confirmed by the clinical history and physical examination (D-H test positive to the right or the left) at the first visit of the study. Those who meet the following three criteria: presenting no exclusion criteria, all inclusion criteria met, and signed informed consent, will be randomized to the intervention group or the control group. Potential participants who fail to comply with the previous three criteria will be declared ‘screening error’.

Patients will be assigned to the intervention or control group using the randomization sequence list prepared in advance by the study statistician. The responsibility for guarding and supervising the randomization list will rest on a staff member of our primary care center who is not directly involved in the trial. GPs will contact the randomization list guardian by telephone in order to find out the randomization number and to which study arm the participant has been assigned. These data will not be recorded in either the case report forms or in the database. Only the study statistician will be allowed access to this information. Follow-up visits will be carried out by a different GP from the one who performed the first visit in order to accomplish blinding of both study participants and personnel. The randomization software used will be ‘R: A language and environment for statistical computing’, version 2.14.2 (R Foundation for Statistical Computing, Vienna, Austria).

### Interventions

A paper case report form (CRF) has been designed to record all the data from the four visits performed during the trial. Once completed, the CRF will be submitted to the study’s coordinator to enable data introduction in the corresponding database for subsequent analysis. The paper case report form will be reviewed after a pilot test.

### Visit 1: Information and data collection from all participants

All participants will have their electronic medical record reviewed. An accurate medical history will be obtained and a thorough physical examination will be performed. The information collected will include: age, sex, educational level, profession and employment status, date of onset and duration of the symptoms from onset to visit 1, previous history of BPPV episodes (total number), past medical history of other conditions (viral infection in the previous four weeks, head trauma, neck osteoarthritis or neck pain), pharmacological treatment, specially for the treatment of anxiety, depression or hypertension).

During the physical examination we will evaluate blood pressure in the sitting and standing positions, heart rate, color of skin and mucous membranes, cardiac and respiratory auscultation, basic neurological examination (cranial nerves, visual fields, brainstem and muscle stretch reflexes, posture, balance and coordination tests (test station, tests for dyssynergia and dysmetria, and gait), otoscopy and D-H maneuver to the left and right to detect the presence of nystagmus or vertigo [22]. If the examination suggests involvement of the anterior or lateral semicircular canals or presence of a central vertigo (nystagmus that lasts more than a minute, vertical nystagmus or alternant), the patient will be excluded from the study and referred to a specialist.

The results of the D-H maneuver (to the right or left) will be divided as follows:

1. Negative.

2. Positive. This result will be subdivided into: a) vertigo with nystagmus or b) vertigo without nystagmus [23].

The assessment of symptom severity will be performed using a 10-point Likert scale, ranging from 0 = no symptoms of vertigo to 10 = most severe and unbearable.

Assessment of quality of life will be carried out through the Dizziness Handicap Inventory-Short form (DHI-S), in an adapted version translated into Spanish by López-Escamez. The adopted version was validated using the translation-back translation method by two interpreters with clinical experience; both translations were then discussed in a consensus meeting with one of the investigators, yielding to the adapted version, which presents a Cronbach’s alpha internal consistency of 0.8014.

The DHI-S is a 10-item self-assessment inventory effectively used to evaluate the perceived degree of disability caused by vertigo, dizziness and instability and its impact on daily life activities. It also identifies physical, functional, and emotional conditions related to balance disorders [24].

### Visit 1 for patients in the intervention group arm

The Epley’s maneuver will be performed only in the first visit since a single procedure has been shown to improve the condition in 76% of patients [25]. Moreover, most patients may improve spontaneously after a month, regardless of which group they were assigned. The maneuver consists of five sequential positions of the head and body, performed with the aim to move the displaced canaliths from the semicircular canal back to the utricle where they no longer cause symptoms. There is some controversy over whether postural restrictions for a few days after this procedure are beneficial for the patient and can improve outcomes [26]. However, we have decided not to include these restrictions in our study as they are poorly tolerated and can hamper the comparability between groups [27].

### Visit 1 for patients in the control group arm

A sham maneuver, which will consist of laying the patient with the head tilted on the affected side for five minutes, as described in the literature [17,23], will be performed only on the first visit.

### Follow-up visits 2, 3 and 4 to all patients

The second visit will take place 1 week after visit 1. Visits 3 and 4 will be performed 1 month, and 1 year after visit 1, respectively. Telephone reminders will be used to reduce patients’ loss during follow-up.

Follow-up visits will include:

•Bilateral D-H maneuver. Outcome measures will be: nystagmus (yes/no) and vertigo (yes/no).

•Assessment and record of number of new episodes of vertigo, and time (in days) from the baseline visit to the first new episode. This information will be obtained through an accurate medical history, and review of the patient’s electronic medical record, including visits to the emergency department, in our medical centers as well as in other emergency centers. Outcome measures will be: vertigo (yes/no), number of episodes, and intensity of symptoms on a 0 to 10-point Likert scale.

•Registration of the total score on the Dizziness Handicap Inventory-Short form (DHI-S)

•Count of tablets of betahistine taken

•Record of new medication taken, for any cause, from visit 1

•Registration of days of temporary disability during the previous year caused by vertigo or any other cause, in employed participants

•Record of medical consultations due to dizziness.

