#### Secondary objectives

We will analyze whether there is a statistically significant clinical improvement in the intervention group in comparison to the control group in terms of:

1. Negativization of the D-H test at a week, a month and a year follow-up.

2. Answer to the dichotomous (yes/no) question regarding presence of vertigo in the previous week.

3. Number of new episodes of vertigo between medical visits.

4. Time from the baseline visit to the first new episode.

5. Rate of vertigo severity on a 10 point-Likert scale: 0 = no symptoms of vertigo; 10 = most severe and unbearable.

6. Quality of life measured with the specific questionnaire Dizziness Handicap Inventory- Short form (DHI-S).

7. Amount of betahistine tablets taken, according to the patients’ self-registers.

8. Days of temporary disability due to vertigo or other causes, recorded on the electronic medical record.

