### Statistical analysis

Data will be analyzed in accordance with the CONSORT guide for cluster randomized trials, and all analyses will be performed on an intent-to-treat basis [28].

Firstly, the intervention group and control group will be analyzed for baseline comparability according to the baseline variables. Descriptive statistics of all studied variables will be presented in contingency tables. Pearson’s Chi-square test or Fisher’s exact test will be applied to assess categorical variables. Student’s *t-*test or ANOVA will be used if the variables follow a normal distribution and Mann–Whitney *U*-test if they do not (objectives 1 and 2).

A multilevel logistic regression analysis will be performed to evaluate the association between the dependent variable (cured/not cured) and the independent variable (group assigned), adjusting potential confounders.

A multivariate linear regression model will be conducted to evaluate change in the Likert scale and quality of life inventory (DHI-S), (objectives 5 and 6); and a Poisson or Binomial negative distribution (for of outcome variables in case of over-dispersion) will be used to compare number of vertigo episodes, number of tablets consumed, days of temporary disability and days with symptoms (objectives 3, 7 and 8).

In order to evaluate D-H test’s intra- and inter-observer variations, corresponding Kappa ponderate indexes (Kp) and intra-class correlation coefficients (ICC) will be calculated. Intra-observer variations will be determined through comparison of the D-H test’s results, performed twice on each patient, after a five-minute interval, for a total number of ten patients per observer, in any visit. Inter-observer variations will be determined through comparison of the D-H test’s results on each patient, conducted by pairs of observers, after a five-minute interval, for a total number of ten patients per pair of observers, in any visit. The estimated number of observers will be 10 to 12. Homogeneity and concordance in the Epley’s maneuver performance will be evaluated by an expert external auditor, who will assess between two and three video-registered maneuvers carried out by each observer.

We will apply the Cox regression model to explore the effect of the intervention (Epley’s maneuver) on the survival (that is interval between two vertigo episodes) (objective 4).

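### The one-year look-back for disability days fits the one-year visit, but at one week and one month over 90% of it lies before randomisation

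*Protocol article*

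**What the plan says.** All references are to the protocol article. The analysis plan is not shown.

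- **Collection.** The section headed "Follow-up visits 2, 3 and 4 to all patients" gives a single list for the three visits. One item is "Registration of days of temporary disability during the previous year caused by vertigo or any other cause, in employed participants". Nothing limits it to visit 4.
- **Timing.** In the same section, "The second visit will take place 1 week after visit 1" and "Visits 3 and 4 will be performed 1 month, and 1 year after visit 1, respectively". The Randomization section places confirmation of the diagnosis and then allocation at the first study visit. The maneuver or sham is given at that visit only.
- **A differently anchored neighbour.** The same list has "Record of new medication taken, for any cause, from visit 1", a window that starts at treatment.
- **Objective.** Secondary objective 8 compares the groups on "Days of temporary disability due to vertigo or other causes, recorded on the electronic medical record". It names no time point and no window.
- **Analysis.** The Statistical analysis section assigns a Poisson or negative binomial model to several counts, among them "days of temporary disability and days with symptoms (objectives 3, 7 and 8". It names no visit, offset or removal of days before randomisation for this outcome.
- **Baseline.** The data listed for visit 1 include employment status but no count of earlier disability days.

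**The concern.** An outcome count should cover time that treatment can affect. A one-year look-back taken one week or one month after treatment consists almost entirely of time before treatment. This is a window the article states, and it does not fit two of the three visits to which it is applied. It is therefore more than a detail left to another document.

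The early visits matter for this outcome. The Hypothesis section claims an effect in the short, mid and long term. The Background expects that remission in the first week may improve temporary disability. The description of visit 1 for the intervention arm says most patients may improve spontaneously after a month. An effect on sick leave is thus most plausible early, where the stated window is least informative.

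Restricting the count to vertigo-related leave would not remove the problem. Symptoms begin before visit 1, and the Study sample section allows up to ten days between the invitation and the baseline visit. Leave from the index episode taken before treatment could still fall inside the window.

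**Working it through.** **The plan's own figure.** The article states no figure for the share of the window before randomisation. The only calculation that touches objective 8 is the sample-size statement (a 1-point difference, standard deviation 1.9, two-sided alpha 0.05, power 0.80). It reproduces: 57 per group, and 57/0.80 = 71.25, so 72 with 20% loss, within the stated 75. It specifies no window, and the present point does not depend on it.

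**Step 1: share of the window before randomisation.** Inputs from the article: look-back 365 days; visits at 7 days, 1 month (taken as 30 days) and 365 days after visit 1; randomisation at visit 1. Formula: (365 − days since visit 1)/365.

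| Visit | Days since visit 1 | Share before randomisation |
|---|---|---|
| 2 | 7 | 358/365 = 98.1% |
| 3 | 30 | 335/365 = 91.8% |
| 4 | 365 | 0/365 = 0% |

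Taking the month as 28 or 31 days gives 92.3% or 91.5%.

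**Step 2: what this does to a rate ratio.** The article gives no disability rates, so everything in this step is assumed. Randomisation makes the expected number of earlier days the same in both arms. Call it P, and let C and T be the expected days after randomisation in the control and treated arms. The windowed ratio is (P + T)/(P + C), which lies closer to 1 than T/C.

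*Illustration A: month 1, true halving from 1.0 to 0.5 days.* P is the assumed number of prior days per year × 0.918.

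- 2 prior days: (1.84 + 0.5)/(1.84 + 1.0) = 0.82
- 5 prior days: (4.59 + 0.5)/(4.59 + 1.0) = 0.91
- 10 prior days: (9.18 + 0.5)/(9.18 + 1.0) = 0.95

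*Illustration B: true ratio 0.50, with the control daily rate after randomisation k times the earlier daily rate.* For d days since visit 1, the windowed ratio is (365 − d + 0.5kd)/(365 − d + kd).

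| k | Visit 2 (d = 7) | Visit 3 (d = 30) | Visit 4 (d = 365) |
|---|---|---|---|
| 1 | 361.5/365 = 0.99 | 350/365 = 0.96 | 0.50 |
| 5 | 375.5/393 = 0.96 | 410/485 = 0.85 | 0.50 |
| 20 | 428/498 = 0.86 | 635/935 = 0.68 | 0.50 |

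**Step 3: direction.** P cancels from the expected difference in days: with 5 prior days, 5.59 − 5.09 = 0.50, the same as 1.0 − 0.5. The absolute difference therefore keeps its expected value but carries the extra variance of the earlier days. The ratio, which a count model with the usual log link estimates, is attenuated. Neither effect creates a benefit where there is none.

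**Step 4: after re-anchoring.** If the window starts at visit 1, its lengths are 7, about 30 and 365 days, and 0% of it precedes randomisation at every visit.

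**The case against.** The strongest reply is that the look-back was written with the one-year visit in mind, where it is exactly right, and that no harm follows elsewhere unless the early counts are analysed. Much of this stands.

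- **Objective 8 as a whole.** A reader might infer that the outcome is compromised altogether. It is not, because the visit 4 window is the follow-up year.
- **Early testing.** The article does not say that disability days are compared at one week or one month. Among the secondary objectives, only the first names the three time points. The primary objective names three visits, but its definition of clinical improvement leaves disability days out. The harm is conditional on the early counts being used.
- **Double counting.** The look-backs overlap, so one might infer that the same days are counted twice. That would need counts to be added across visits, and the article nowhere says they are.
- **Mixing causes.** One might infer that vertigo leave and other leave are pooled. The wording is equally compatible with recording days by cause.
- **No visible effect.** One might infer that the early comparisons would show nothing. The illustrations show attenuation of varying degree on assumed rates, which is a weaker statement.
- **Recoverability.** The electronic medical record is the named source. If it holds leave dates, days since visit 1 can be derived. The case report form was also to be reviewed after a pilot test.

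What does not stand is the suggestion that nothing needs correcting. The text applies the item to visits 2 and 3 without exception, and its neighbour in the list shows that a window from visit 1 was available. No baseline count is listed that could be subtracted or adjusted for.

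**Conclusion.** The point holds in a limited form. As written, the disability item at visits 2 and 3 collects a count of which about 98% and 92% of the window precedes randomisation. These shares follow from the article alone. The window at visit 4 is sound.

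Any one-week or one-month comparison based on these counts would have its rate ratio diluted towards 1 and its variance increased, with no bias towards a false benefit. The size of the dilution rests on assumed rates. For a true ratio of 0.50, the illustrations give 0.68 to 0.96 at one month and 0.86 to 0.99 at one week.

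This concerns one of eight secondary objectives, in employed participants only, and it does not affect the sample size. It is worth correcting because the error is clear and the correction is simple.

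**What to change.** Reword the item so that disability days are counted from visit 1 to each follow-up visit, matching the new-medication item, and derive them from leave dates in the electronic medical record.

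Optionally, record the disability days in the year before visit 1 once, at baseline, and use them as a covariate in the count model. This could recover precision but is not needed to correct the error. Whether vertigo-related or all-cause days should be the main measure is a matter of preference and can be settled separately.

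The cost is wording on the case report form. The source is already named, and no visit or procedure is added. This assumes that the record holds the start and end dates of leave, which should be confirmed.

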### Statistical analysis

Data will be analyzed in accordance with the CONSORT guide for cluster randomized trials, and all analyses will be performed on an intent-to-treat basis [28].

Firstly, the intervention group and control group will be analyzed for baseline comparability according to the baseline variables. Descriptive statistics of all studied variables will be presented in contingency tables. Pearson’s Chi-square test or Fisher’s exact test will be applied to assess categorical variables. Student’s *t-*test or ANOVA will be used if the variables follow a normal distribution and Mann–Whitney *U*-test if they do not (objectives 1 and 2).

A multilevel logistic regression analysis will be performed to evaluate the association between the dependent variable (cured/not cured) and the independent variable (group assigned), adjusting potential confounders.

A multivariate linear regression model will be conducted to evaluate change in the Likert scale and quality of life inventory (DHI-S), (objectives 5 and 6); and a Poisson or Binomial negative distribution (for of outcome variables in case of over-dispersion) will be used to compare number of vertigo episodes, number of tablets consumed, days of temporary disability and days with symptoms (objectives 3, 7 and 8).

In order to evaluate D-H test’s intra- and inter-observer variations, corresponding Kappa ponderate indexes (Kp) and intra-class correlation coefficients (ICC) will be calculated. Intra-observer variations will be determined through comparison of the D-H test’s results, performed twice on each patient, after a five-minute interval, for a total number of ten patients per observer, in any visit. Inter-observer variations will be determined through comparison of the D-H test’s results on each patient, conducted by pairs of observers, after a five-minute interval, for a total number of ten patients per pair of observers, in any visit. The estimated number of observers will be 10 to 12. Homogeneity and concordance in the Epley’s maneuver performance will be evaluated by an expert external auditor, who will assess between two and three video-registered maneuvers carried out by each observer.

We will apply the Cox regression model to explore the effect of the intervention (Epley’s maneuver) on the survival (that is interval between two vertigo episodes) (objective 4).

Statistical analysis will be carried out by statisticians from the Institut Universitari d’Investigació en Atenció Primària Jordi Gol (IDIAP Jordi Gol), who will have an advisory role. Data will be introduced into a SPSS version 18.0 system database (SPSS Inc, Chicago, IL, USA). Descriptive analysis, and statistical hypothesis testing, will also be conducted with the SPSS version 18.0 system, with blinding. The level of statistical significance will be set at 0.05 and all tests will be two-tailed. All known potential confounding factors will be measured at the beginning of the study and comparison between the control and the intervention groups will be carried out adjusted for these known confounders.

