### Sample size

Accepting an alpha risk of 0.05 and a beta risk of 0.2 in a bilateral contrast, sample size calculations determined a need for approximately 75 subjects in each group (the intervention group and the control group), in order to detect a statistically significant difference in the improvement rate between the two groups (30% for the control group and 55% for the intervention group) at follow-up. We estimated a 20% rate of loss in participants (objectives 1 and 2). This sample size also enables us to evaluate 1-point clinical improvement in the intervention group compared to the control group, assuming a standard deviation of 1.9 (objectives 3,5,6,7 and 8). We estimated a recurrence hazard ratio of 0.5 in the intervention group, assuming that 30% of patients in the control group will have relapsed after one year. The software used for the calculation was GRANMO version 7.12. The software used for the calculation was GRANMO version 7.12 (Program of Research in Inflammatory and Cardiovascular Disorders. Institut Municipal d’Investigació Mèdica, Barcelona, Spain).

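### Objectives 5 and 6: naming the visit 1 score as a covariate in the change models would be a free gain in precision

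*Protocol article*

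**What the plan says.** All places are in the protocol article.

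- **Outcome and model (Statistical analysis).** "A multivariate linear regression model will be conducted to evaluate change in the Likert scale and quality of life inventory (DHI-S"). The sentence covers objectives 5 and 6 and names no covariate.
- **General adjustment rule (end of Statistical analysis).** Known potential confounders are measured at the start, and "comparison between the control and the intervention groups will be carried out adjusted for these known confounders". No list is given. The one adjustment variable named in the article is the observer, which Study limitations assigns to the multilevel logistic model.
- **Baseline data (Visit 1: Information and data collection from all participants).** "The assessment of symptom severity will be performed using a 10-point Likert scale", running from 0 to 10, and the DHI-S is completed at the same visit. Both scales are recorded again at visits 2, 3 and 4.
- **Role of the two scales (Primary objective).** Perceived vertigo and quality of life are part of the definition of clinical improvement, so these outcomes are not peripheral.
- **Planning assumptions (Sample size).** The same sample is said to allow detection of a "1-point clinical improvement in the intervention group compared to the control group" with an SD of 1.9. The section does not say whether 1.9 is the SD of a score or of a change.

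**The concern.** A patient's own starting score is usually a strong predictor of the later score on the same scale. In a randomised trial it is a prognostic covariate and need not count as a confounder, so a rule limited to known confounders does not clearly bring it into the model.

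Subtracting the baseline is not the same as adjusting for it. Subtraction fixes the baseline slope at 1, whatever the data show. When the true slope is below 1, the change score overcorrects. It carries extra baseline variability, and any chance difference between the groups at visit 1 feeds into the treatment estimate through regression to the mean. This is plausible here, because patients enter with a positive Dix-Hallpike test and the article expects that most may improve spontaneously within a month.

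At stake is the precision of the treatment estimate on two patient-reported scales that belong to the primary objective.

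**Working it through.** **1. The plan's own figure.** The inputs, all from Sample size, are: "Accepting an alpha risk of 0.05 and a beta risk of 0.2 in a bilateral contrast"; "30% for the control group and 55% for the intervention group"; and 20% loss. The pooled two-proportion formula gives 61 per group, and 61/0.8 = 76.25, so 77. The unpooled formula gives 58, inflated to 73. The arcsine formula gives 60, inflated to 75. The stated "approximately 75 subjects in each group (the intervention group and the control group") is therefore reproduced.

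For a 1-point difference with SD 1.9:

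n = 2 × (1.960 + 0.842)² × 1.9² / 1² = 56.7, so 57 per group, and 57/0.8 = 71.25, so 72.

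Seventy-five covers this. With 75 × 0.8 = 60 completers per group, power is 82.2%.

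**2. Variance with and without the baseline score.** Let r be the within-group correlation of baseline and follow-up, and k the baseline SD divided by the follow-up SD. In units of the follow-up variance:

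- unadjusted change: 1 + k² − 2rk
- with baseline as covariate: 1 − r²
- difference: (k − r)², which is never negative

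In large samples, adding the baseline score therefore cannot lose precision relative to unadjusted change. In this trial it uses one degree of freedom out of about 120 completers.

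**3. Equal SDs (k = 1, an assumption).** The ratio becomes (1 − r²)/(2(1 − r)) = (1 + r)/2. The documents give no r, so a range is shown. Power is for a 1-point difference with 60 completers per group.

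| Assumed r | Variance ratio | 1.9 is SD of change: unadjusted → with baseline | 1.9 is SD of a score: unadjusted → with baseline |
|---|---|---|---|
| 0.2 | 0.60 | 82.2% → 96.1% | 62.5% → 83.7% |
| 0.5 | 0.75 | 82.2% → 91.4% | 82.2% → 91.4% |
| 0.8 | 0.90 | 82.2% → 86.0% | 99.5% → 99.8% |

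Worked case, first row, 1.9 as SD of change: the residual SD is 1.9 × √0.60 = 1.472; 1/(1.472 × √(2/60)) = 3.72; 3.72 − 1.96 = 1.76, which gives 96.1%.

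**4. Unequal SDs.** At r = 0.5 and k = 0.5 the ratio is 0.75/(1 + 0.25 − 0.5) = 1.00, so there is no gain. At r = 0.5 and k = 1.5 it is 0.75/(1 + 2.25 − 1.5) = 0.43, a larger gain than under equal SDs.

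**5. Chance imbalance.** With equal SDs the true baseline slope is r. For each point by which the groups happen to differ at visit 1, the unadjusted change estimate moves by 1 − r points in the opposite direction: 0.8, 0.5 or 0.2 points at r = 0.2, 0.5 or 0.8.

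**6. Change or follow-up score as the outcome.** Change is follow-up minus baseline. If baseline is already a covariate, subtracting it only lowers its own coefficient by 1; the group coefficient and residuals do not move. A simulated data set confirmed this: both forms gave an effect of −1.182 with standard error 0.2470.

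**The case against.** The strongest reply is that silence is not exclusion. The model is called multivariate, which may simply mean several covariates. The article also promises adjustment for factors measured at the start, and the visit 1 scores could be among them. The document is a journal article, and a covariate list is commonly left to the full protocol or the analysis plan, neither of which is shown. This stands: the missing list is not in itself a fault.

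It is also true that change is a legitimate outcome, that the comparator in the calculation has no covariates whereas the article plans some adjustment, and that both r and the equality of the SDs are assumed. Other baseline factors in the model might already capture part of the gain. These points stand too, and they limit how firmly the gain can be quantified.

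A reader might infer more than the documents support:

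- **That the plan analyses these scales without the baseline score.** No sentence says so.
- **That the estimate would be biased.** Randomisation keeps even the unadjusted comparison of change unbiased over repeated allocations.
- **That the sample size is wrong.** It reproduces on its own terms. The 62.5% in the table needs three things together: 1.9 as the SD of a single score, a low correlation, and no baseline covariate. The documents establish none of them.

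What the reply does not remove is that the text, as it stands, does not secure adjustment for the baseline score. A rule framed around confounders leaves a prognostic baseline score open to either reading.

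**Conclusion.** The point holds as a free improvement. The article fixes change as the outcome for objectives 5 and 6 and leaves open whether the visit 1 score enters the model.

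If it does not, the cost is in precision and in dependence on chance imbalance. Compared with unadjusted change, including the score multiplies the variance of the treatment effect by 0.60 to 0.90, a reduction of 40% to 10%. This assumes equal SDs and r of 0.2 to 0.8. With unequal SDs the reduction can be larger, or nil when k equals r. If the score is already meant to be included, nothing is lost and the sentence only needs to say so.

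**What to change.** State in the analysis plan, before unblinding, that the linear models for objectives 5 and 6 include the visit 1 score of the same scale as a covariate: visit 1 severity for severity, visit 1 DHI-S for DHI-S. The outcome may stay as change or become the follow-up score.

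One linear mixed model over visits 2 to 4, with group, visit, their interaction and the visit 1 score, is an option but is not needed to settle this point.

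The cost is one sentence. No new data, visits or patients are required, because both scores are already collected at visit 1.

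### The Cox model for objective 4 is defined on the interval between two vertigo episodes, but objective 4 and the data collected run from the baseline visit to the first new episode

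*Protocol article*

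**What the plan says.** Four places in the protocol article bear on the recurrence endpoint.

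- Secondary objectives, item 4: "Time from the baseline visit to the first new episode".
- Follow-up visits 2, 3 and 4: the items to be recorded include "time (in days) from the baseline visit to the first new episode" and the number of new episodes. No interval between episodes is listed.
- Sample size: recurrence is planned with a hazard ratio of 0.5 and 30% of control patients relapsed by one year.
- Statistical analysis: the Cox model is to explore the effect of the maneuver on "survival (that is interval between two vertigo episodes) (objective 4").

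The Statistical analysis section also states that "all analyses will be performed on an intent-to-treat basis". The Randomization section places allocation at the baseline visit (visit 1).

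**The concern.** One numbered objective has been given two different clocks. The first three places describe a time-to-first-recurrence endpoint measured from randomisation in everyone randomised. The fourth, the only one that tells the analyst what to model, describes a gap between episodes.

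The time origin of a Cox model decides who is at risk and when. If the gap lies between two post-baseline episodes, a patient enters only after relapsing, and relapse is what the maneuver is meant to prevent. The arms being compared would then no longer be the arms that were randomised. If the gap runs from the index episode, nobody is lost, but the clock starts before allocation. In neither case is the quantity estimated the one named in objective 4.

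**Working it through.** **1. The plan's own figure.** Sample size gives "Accepting an alpha risk of 0.05 and a beta risk of 0.2 in a bilateral contrast", improvement of "30% for the control group and 55% for the intervention group", and "We estimated a 20% rate of loss in participants", leading to "approximately 75 subjects in each group". By the arcsine formula, n = 2(1.960 + 0.842)² / h², with h = 2·asin(√0.55) − 2·asin(√0.30). This gives 59.96 per group, and 59.96 / 0.8 = 74.95, so 75. The pooled-variance formula gives 61, or 77 after loss. The 75 is therefore reproduced. It comes from a binary endpoint and does not depend on how the Cox outcome is defined.

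**2. Patients expected to relapse within a year.** Inputs from Sample size: control risk 0.30, hazard ratio 0.5. Under proportional hazards the intervention risk is 1 − (1 − 0.30)^0.5 = 1 − 0.8367 = 0.163.

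| | Control | Intervention | Total |
|---|---|---|---|
| 75 per group, no loss | 75 × 0.30 = 22.5 | 75 × 0.163 = 12.3 | 34.8 of 150 |
| 60 per group, after 20% loss | 60 × 0.30 = 18.0 | 60 × 0.163 = 9.8 | 27.8 of 120 |

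**3. Who enters the model under each definition.**

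- *Baseline visit to first new episode (objective 4).* All 150 randomised patients enter, and those with no new episode are censored. The 28 to 35 relapses are the events.
- *Gap between two post-baseline episodes.* Only those 28 to 35 patients enter. They are 27.8 / 120 = 23% of the sample, split 18.0 : 9.8, or about 65 : 35. Patients with no new episode never appear.
- *Onset of the index episode to the next episode.* All patients enter. The clock starts at symptom onset, which visit 1 records as an earlier date, so time before visit 1 counts as follow-up that is event-free by construction. That extra time cannot depend on allocation.

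**4. What the post-baseline gap could do to the estimate.** This is a simulation, and its assumptions are not in the document: constant hazards over one year, gamma frailty with variance 0 to 4, and a conditional hazard ratio of 0.5 to the first episode.

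- If the effect does not carry past the first recurrence, the rate ratio for the gap is 0.99 to 1.17, against 0.50 to 0.65 for time to first episode.
- If the effect persists, the gap ratio is 0.50 to 0.68, close to the first-episode ratio, but it rests on about 5 to 19 second episodes in 150 patients.

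**The case against.** The best defence is that the parenthesis is loose wording. The model is tagged to objective 4, the data to be recorded match objective 4, the planning assumptions describe relapse by one year, and intent-to-treat is stated for every analysis. Each participant also enters with an index episode, so an interval between two episodes most naturally means index to next, which keeps everyone in. This largely stands. The selection described above arises only if both episodes are post-baseline, which is the less plausible reading. The defence does not remove the mismatch, because even the favourable reading gives a different time origin from objective 4.

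The stakes are also limited. Recurrence time is one of eight secondary objectives, it is not part of the primary definition of clinical improvement, and the Cox model is described as exploratory.

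A reader might go further and infer that patients who never leave the index episode will be counted as recurrence-free, that this biases the result against the Epley group, and that a failure-or-recurrence composite is therefore needed. The article does not support this. It states no counting rule for unresolved index episodes, and such a rule commonly sits in a fuller document. The size of any bias also depends on assumed figures. Take persistence at one month of 33% under sham and 15% under Epley, with 30% annual relapse among remitters in both arms:

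- If persisters are never at risk all year, apparent recurrence is 0.67 × 0.30 = 0.201 against 0.85 × 0.30 = 0.255, a spurious ratio of ln(0.745) / ln(0.799) = 1.31.
- If persisters become at risk on remitting at 2, 3 or 6 months, the ratio is 1.03, 1.05 or 1.11.

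The Background gives an average episode of two weeks, and the visit 1 text for the intervention arm expects most patients may improve within a month. Both point to the lower end. A composite would also replace the stated objective with another and overlap objectives 1 and 2.

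**Conclusion.** The contradiction is explicit and unresolved, and the Cox outcome is wrong as written. The consequence depends on the reading. A post-baseline gap would restrict the analysis to about 28 of 120 patients, chosen by a post-randomisation event and against the plan's own intent-to-treat statement. An index-to-next interval keeps all patients and only misplaces the time origin.

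The 28 of 120 rests on the plan's 30% control relapse, hazard ratio of 0.5 and 20% loss, with proportional hazards and equal loss in the two groups assumed here.

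A reader might infer that the randomised comparison of recurrence is already lost. The document does not support that: the endpoint data are to be collected correctly, and only the analysis sentence needs to match them. This is a wording correction to a secondary analysis and does not touch the primary objective or the 75 per group.

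**What to change.** In Statistical analysis, replace the parenthesis that defines survival with: *time from the baseline visit (randomisation, visit 1) to the first new episode, in all randomised patients, censored at last follow-up*.

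The cost is one sentence. The follow-up visits already record the required number of days, so no new data are needed and the sample size stays as it is. The change should be made before the data are analysed. Objective 4 should remain the endpoint as stated, without a failure-or-recurrence composite in its place.
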